### Measurements

Table 1 shows an overview and time schedule for data to be collected in the intervention study (e-VitaDM) and the observational cohort study (ZODIAC). The collection of data follows NEN-procedure 7510 and all substandards based on the ISO 27000 series. In addition, all identifiable personal information will be encrypted in accordance with the Rijndael algorithm.

**Table 1 T1:** Overview and time schedule for data to be collected

	**Patients using platform (e-VitaDM)**				**Patients in cohort only (ZODIAC)**			
	**T-1**	**T0**	**T1**	**T2**	**T-1**	**T0**	**T1**	**T2**
Patient profile		X				X		
Use of platform			X	X				
EQ-5D, EQ-VAS, WHO-5, PAID-5,		X	X	X		X	X	X
SDSCA	X			X	X			X
Europep								
Laboratory/clinical measures		X		X		X		X
Medication care utilization		X	X	X		X	X	X
Micro- and macrovascular complications		X		X		X		X
Mortality, assessed by PN/GP				X				X
Number of encounters with care providers				X				X
Mortality, CBS, GBA				X				X

The baseline assumption is that ≥90% will participate in the long-term study (ZODIAC), as was our experience in the earlier ZODIAC-study, but that no more than 20% of the patients will express interest in the e-Vita platform (e-VitaDM).

#### Quality assessment lists

All patients with T2DM participating in the observational cohort study (including those who are not interested in the platform) are asked to fill in a range of validated questionnaires to measure perceived quality of life (EQ-5D) [13], well-being (WHO-5) [14], diabetes-distress (PAID-5) [15], diabetes self-care behaviour (SDSCA) [16] and perceived quality of received care (Europep) [17,18]. Additional questions about coffee/tea intake, smoking habits, employment and educational background are included as well. Questionnaires are filled in at different time points (see Figure 3).

#### Clinical data gathering

Besides the questionnaires, clinical measures as described in the NHG/NAD core set of parameters will be collected (see Additional file 2). These measures are already being collected by the patients’ GP and PN during their annual check-up and are routinely sent to our Diabetes Centre for benchmark en study purposes. After informed consent of included patients, clinical data will be combined with the results of the collected questionnaires to assemble a complete and anonymized dataset. Data regarding micro- and macrovascular complications and mortality will be gathered from patient records from the GP. Mortality will also be checked by using data from Central Statistical Office (in Dutch: Centraal Bureau voor Statistiek (CBS)) or Municipal Administration (in Dutch: Gemeentelijke Basisadministratie (GBA)).

#### Data on actual contacts

Data on actual amount of patient – care provider contacts will be retrieved in a subpopulation. The availability of these data greatly depends on the information system used by primary care givers. Since five different systems (each with their own strengths and limitations) are used in the Drenthe-region, one specific information system (Medicom, which is used by 8 general practices) is chosen for detailed analysis on this subject. This system is not only known for its reliability of structured data entry, data transport and medication information, but especially for its reliable registration of number of encounters with care providers and number of hospitalizations.

#### Further sample collection and storage

In addition to the blood drawn as part of the annual check-up, two extra tubes of blood (10 ml serum and 10 ml plasma) will be collected in consenting subjects and frozen for future research on novel biomarkers.

#### Assessment of determinants of platform use

In order to find out how the platform is used in practice, log-data will be used to track individual use of the platform over time (number of log-ons, time spent per session and used elements). These log-files will be used for identifying user profiles and they will provide insight about adherence to the platform, usage patterns and what elements of the platform are used. This information provides insight in how the platform (both content and system) matches with the users [26]. In addition, specific questionnaires will be sent to all patients who expressed their interest in using the e-Vita platform, irrespective of actual use. These questionnaires include TIPI [27], PAM-13 [28], short version of PII [29], questions about trust [30], questions about general use of the Internet and questions about use of and satisfaction with the platform [31].

Furthermore, care providers will be interviewed in a semi-structured way to assess possible care provider related factors influencing patient’s platform use.

### Primary and secondary endpoints

The quality assessment in terms of EQ-5D is the primary objective in this study. A clinically relevant difference of 0.074 in the EQ-5D index score is predefined [32]. Secondary endpoints are well-being as assessed by the WHO-5 questionnaire, diabetes-distress as assessed by the PAID-5, self reliance as assessed by the SDSCA, quality of delivered care as assessed by the Europep and clinical parameters.

### Statistical analyses

#### Analyses in intervention study (e-VitaDM)

To evaluate differences in target variables over time and within groups, we will use the linear mixed model for repeated measures. Variables measured after 6 and after 12 months will be used as within-subjects variables. Baseline variables will be used as covariates. Making use of the platform or not will be used as a between-subjects factor. In case of differences between groups on relevant variables, these variables will be added as a covariate in the multivariable analyses.

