## Methods

### Study design

A prospective observational study of patients volunteering to use the interactive care platform (e-VitaDM), within the ZODIAC study (see Figure 1). Nested in this observational study a randomized controlled trial is planned testing coaching vs. non-coaching of a self-management support module (see Figure 2) [12].

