### Setting

The CGD is one of the care groups connected to our Diabetes Centre for benchmarking and study purposes for years. It is the largest care group in The Netherlands, including over 500,000 subjects and over 200 GP’s, divided over 110 practices. 52 out of the 110 general practices agreed to participate in the e-VitaDM/ZODIAC study. In these practices approximately 8300 T2DM patients were treated in 2011.

In line with clinical guidelines, patients in CGD are seen four times a year, of which one visit is the annual check-up. All patients with T2DM fulfilling the inclusion criteria, will be asked to participate in the prospective observational cohort study (ZODIAC) three months before their annual check-up. They are also informed about the possibility to use the care platform (e-VitaDM). Patients who express interest in using the platform are registered on the platform by their primary care nurse (PN) and will be included in the e-VitaDM study. The PN’s are trained to offer their T2DM patients information and guidance with the use of the platform and its educational content. Participants will be able to use the platform after their written consent and registration by their PN.

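### Covariates enter the e-VitaDM model only when the self-selected groups are seen to differ; the adjustment set should be fixed in advance from pre-exposure variables

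*Protocol article*

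**What the plan says.** The Study design section of the protocol article describes "A prospective observational study of patients volunteering to use the interactive care platform (e-VitaDM), within the ZODIAC study". Under Setting, a patient joins the platform group by expressing interest and is then registered by the practice nurse. The contrast is therefore self-selected.

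The section on analyses in the intervention study sets out a linear mixed model with the 6- and 12-month values as repeated outcomes and platform use as the between-subjects factor. On adjustment it says two things: "Baseline variables will be used as covariates", and "In case of differences between groups on relevant variables, these variables will be added as a covariate in the multivariable analyses". It defines neither a relevant variable nor a difference.

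The Objectives section states the hypothesis in causal terms: platform use is expected to improve quality of life. EQ-5D is primary, with 0.074 index points predefined as clinically relevant.

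**The concern.** In a non-randomised comparison that tests a causal hypothesis, covariate adjustment is the main protection against bias. The nested randomised trial compares coaching with no coaching, so it does not protect the user versus non-user contrast.

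The stated rule has three weaknesses:

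- **It asks the wrong question.** Whether a difference is seen depends on sample size as well as on its magnitude. A variable needs adjustment if it is related to both platform use and outcome, and an observed difference speaks only to the first.
- **It settles the model after the data are seen.** With both key terms undefined, different covariate sets, possibly a different one for each outcome, would all comply.
- **It does not restrict timing.** A variable that platform use itself changed could enter as a covariate and remove part of the effect under study.

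At stake is whether a small but significant EQ-5D difference can be read as an effect of the platform. In so large a comparison, a small bias is enough for significance.

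**Working it through.** The article states no sample size, alpha, SD or correlation, so there is no figure of its own to reproduce.

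**Inputs from the article**
- Setting: "In these practices approximately 8300 T2DM patients were treated in 2011".
- Measurements: at least 90% expected in the cohort, 8300 × 0.90 = 7470.
- Measurements: at most 20% interested in the platform. Taken of the cohort, 7470 × 0.20 = 1494 users v 5976 non-users. Taken of all patients, 8300 × 0.20 = 1660 v 7470 − 1660 = 5810. Both are upper bounds on users.
- Clinically relevant difference: 0.074.

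**Assumptions**
- Two-sided 5% test, EQ-5D SD 0.20 (range 0.15 to 0.30), baseline-to-follow-up correlation r of 0.5 to 0.7, and full retention unless stated.

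**Step 1: precision.** SE = SD × √(1 − r²) × √(1/n₁ + 1/n₂); half-width = 1.96 × SE. With SD 0.20:

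| Users v non-users | √(1/n₁ + 1/n₂) | r | SE | Half-width |
|---|---|---|---|---|
| 1494 v 5976 | 0.0289 | 0.5 | 0.0050 | 0.0098 |
| 1494 v 5976 | 0.0289 | 0.7 | 0.0041 | 0.0081 |
| 1660 v 5810 | 0.0278 | 0.5 | 0.0048 | 0.0094 |
| 1660 v 5810 | 0.0278 | 0.7 | 0.0040 | 0.0078 |

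Over SD 0.15 to 0.30 the half-width at 1494 v 5976 runs from 0.006 to 0.015.

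**Step 2: what a residual bias b does under no effect.** Chance of p<0.05 = 1 − Φ(1.96 − b/SE) + Φ(−1.96 − b/SE). At 1494 v 5976:
- SD 0.20, b = 0.010: 51% (r = 0.5) to 68% (r = 0.7).
- SD 0.20, b = 0.020: 98% to over 99%.
- SD 0.30, r = 0.5: 26% at b = 0.010 and 76% at b = 0.020.

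Lost follow-up weakens this. At 1660 v 5810, SD 0.20 and r = 0.6, the chances are 61% and 99% with full retention, and 36% and 89% with half retained.

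Against the margin, 0.010/0.074 = 14% and 0.020/0.074 = 27%.

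**Step 3: what the rule itself contributes.** Null simulations used 1660 v 5810, SD 0.25, r = 0.6, five measured confounders each with an effect of 0.1 SD on the outcome, a p<0.05 entry screen and 400 replicates (Monte Carlo standard error near a 5% rate: √(0.05 × 0.95/400) = 1.1 points). False-positive rates:

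| Group difference per confounder | Baseline EQ-5D only | Stated rule | Fixed set |
|---|---|---|---|
| 0.03 SD | 12% | 8% | 5% |
| 0.10 SD | 63% | 4% | 4% |
| 0.20 SD | 98.5% | 7% | 7% |

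With an added unmeasured bias of 0.015 (group difference 0.1 SD, confounder effects 0.05 SD), the rule gave 77% and the fixed set 76%. Stronger confounder effects than those tried would widen the gap in the first row.

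**Step 4: lower uptake.** Detection of a 0.10 SD imbalance by a p<0.05 screen = Φ(0.10/√(1/n₁ + 1/n₂) − 1.96):
- 20% uptake (1494 v 5976): Φ(3.46 − 1.96) = 93%.
- 10% uptake (747 v 6723): Φ(2.59 − 1.96) = 74%.
- 5% uptake (374 v 7096): Φ(1.88 − 1.96) = 47%.

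At 5% uptake such a confounder would be left out about half the time. The interval is also wider there, so the error rate need not rise in proportion.

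**The case against.** The strongest case against the point is that the rule hardly changes the error rate. At the expected size it admits nearly every measured confounder that differs by 0.1 SD or more, and then performs like a fixed set. That stands. The case for change rests on discretion, timing and low uptake, not on a large gain in type I error.

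A second objection is that an article leaves covariate lists to the full protocol or analysis plan. For the list itself that is fair. But the article states a rule for entry, and that rule makes the list depend on the data.

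A reader might also go further in four ways that the documents do not support:

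- **That a null platform would be declared effective.** If T0 EQ-5D were the only adjuster, a stable group gap d₀ would leave (1 − r) × d₀. With SD 0.20 and 1494 v 5976, d₀ = 0.03 and r = 0.7 leave 0.009 (59% chance of p<0.05), and d₀ = 0.05 and r = 0.5 leave 0.025 (over 99%). But the plan adjusts for baseline variables in the plural and adds others, and no gap is given. With r = 0.7, d₀ = 0.01 gives only 11% and d₀ = 0.02 gives 31%.
- **That using baseline as a covariate is an error.** It is a standard choice; it is only insufficient alone under self-selection.
- **That the bias exceeds the confidence interval.** A bias of 0.009 exceeds the half-width of 0.0081 but not the full width of 0.016.
- **That the rule fails in the eight-practice subset.** The article assigns that subset to care-contact data; EQ-5D is collected across the whole cohort.

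**Conclusion.** The point holds as a correction to a stated analysis rule. Covariate entry that depends on observed group differences is a poor basis for adjustment in a self-selected comparison, and the wording leaves room for choices made after seeing the data and for covariates measured after exposure.

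The size is conditional. At the expected upper-bound numbers, a residual bias of 0.01 to 0.02 EQ-5D points could reach p<0.05 without any platform effect. SD, correlation, retention and the amount of confounding are assumptions, since the article gives none of them. Such a bias is 14% to 27% of 0.074, so reading the result against that margin would guard against a false claim of clinical relevance; the analysis section does not tie the conclusion to it.

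The rule's own share of the error was modest in the scenarios tried. Most of the exposure comes from differences that no measured covariate captures. Personality, patient activation, trust and internet use are examples: the section on determinants of platform use collects them only from patients who expressed interest, so they cannot be adjusted for across the groups.

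**What to change.** Replace the conditional sentence with one covariate set, fixed before outcome data are examined, chosen on subject-matter grounds, measured at or before T0 and used for every outcome. Candidates are age, sex, education, employment, smoking, medication, complications, HbA1c, baseline questionnaire scores where collected, and practice. The article shows most of these being collected; the questionnaire scores need checking against Table 1, which as extracted does not mark every instrument at T0.

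Keep the baseline-as-covariate mixed model as the main analysis. As a sensitivity analysis, report a model with T0, 6 and 12 months all as responses and a group-by-time term. It removes a stable group difference that covariate adjustment may remove only in part, but it assumes that the groups would have followed parallel trends without the platform, and that should be stated.

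Interpret the estimate and its confidence interval against 0.074, not by p<0.05 alone.

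The cost is a change of wording, modest programming, a slightly wider interval and one more reported model. None of this removes unmeasured confounding, and the report should say so.

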#### Additional analyses in larger prospective cohort study (ZODIAC-40)

Cox proportional hazard models will be used to investigate the association between (bio)marker levels and future events (microvascular complications, macrovascular complications and mortality) with adjustment for selected confounders.

Harrell’s C statistic, a rank based measure will be used to compare how well the presence of the marker in the different models used, predicts the outcome of interest.

The need for additional analyses, i.e. measures of discrimination improvement (integrated discrimination improvement, IDI, and net reclassification improvement, NRI) will be decided for each marker separately.

### Medical ethical committee

The current study has been reviewed and approved by the Medical Ethical Committee of Isala.

## Discussion

Offering T2DM patients information, education and insight in health data through internet is not new at all. However, to our knowledge, in The Netherlands there has never been a study of the proposed scale towards feasibility, efficiency and the effects of an interactive care platform as proposed in the e-Vita research program. Furthermore, part of the assessment includes structural measurements of perceived quality of life and care.

At the start of e-VitaDM study the actual content of the care platform is limited to insight in DM-related health data of an individual patient and education. In this ongoing study, new modules will be added especially concentrating on educational content. The development of further educational content is crucial, not only to further enhance active use of the platform, but also to assess the effects of new additions and improvements in a continuous cycle using focus groups in each step. The creation of content, including 2-way communication, e-contact and e-consult, during this study and keeping track of its fit with patients’ needs is not the primary focus in this research, but nevertheless has to be taken into account, not only in striving for the largest possible effect, but also in analyzing the collected data. At the moment, communication between PN’s and patients is limited to automated messages in the electronic patient record when patients allow this in case of completing educational modules. The platform does not provide an extensive 2-way communication tool (e.g. exchange messages) on top of the automated messages, but developments concerning this are already ongoing.

A previous study by the British National Health System proves that unless personal electronic health records align closely with people’s attitude, self management practices, identified information needs and the wider care package (including organizational routines and incentive structures for clinicians), the risk that they will be abandoned or not adopted at all is substantial [33].

The WSD shows that telehealth is associated with lower mortality and emergency admission rates [34], but also that telehealth did not improve quality of life or psychological outcomes for patients with COPD, T2DM or CHF over 12 months [35]. In terms of cost-effectiveness, the WSD shows that the QALY gain by patients using telehealth in addition to usual care was similar to that by patients receiving usual care only, and total costs associated with telehealth were higher [6]. However, generalizability of the WSD-study results in terms of diagnosis, relative risks and outcomes to the Dutch situation in uncertain.

## Abbreviations

CBS: Central Statistical Office (in Dutch: Centraal Bureau voor de Statistiek); CGD: Care Group Drenthe; CHF: Chronic heart failure; COPD: Chronic obstructive pulmonary disease; EQ-5D: EuroQol – 5 dimensions; GBA: Municipal Administration (in Dutch: Gemeentelijke Basisadministratie); GP: General Practitioner; HRQoL: Health related quality of life; ICPC: international classification of primary care; LSD: Large scale demonstrator; NAD: National action program Diabetes (in Dutch: Nationaal Actieprogramma Diabetes); NHG: Dutch GP Society (in Dutch: Nederlandse Huisartsen Genootschap); PAID-5: Problem areas in diabetes – 5 questions; PAM-13: Patient activation measure – 13 questions; PII: Personal involvement Inventory; PN: Primary care nurse; QALY: Quality adjusted life years; SAL: Security access layer; SDSCA: Summary of diabetes self-care activities; T2DM: Type 2 diabetes mellitus; TIPI: Ten-item personality inventory; WBP: Personal Data Protection Act (In Dutch: Wet Bescherming Persoonsgegevens; WHO-5: WHO – Five item measure of well being; WSD: Whole system demonstrator; ZODIAC: Zwolle outpatient diabetes project integrating available care.
